### Sample size

An improvement of either or both of the primary outcomes, i.e. cancer-related physical fatigue or HRQoL, from baseline to 6 months post-baseline relative to control is of relevance. To adjust for multiple testing, the Bonferroni-Holm method will be used. Based on results from 6 randomized exercise trials in patients with breast cancer receiving adjuvant treatment, we anticipate an effect size of 0.35, which has been found in a pooled analysis [35]. With *n*=139 patients per group (*n*=278 in total), for each endpoint separately a mean standardized effect size of at least 0.35 can be detected with an analysis of covariance (ANCOVA) adjusted for baseline values of the outcome with a power of at least 78% or 82% at a (nominal) two-sided significance level of 2.5%, assuming a correlation between pre- and post-intervention levels of Rho=0.3 or Rho=0.4, respectively [36]. However, the probability of at least one of the two tests corresponding to the two primary outcomes to yield a significant result, if both alternative hypotheses are true, is higher. In addition, taking repeated measures into account using mixed models might further increase the study power. To account for a potential drop-out rate of approximately 20%, a total number of *n*=350 patients will be enrolled into the study (*n* = 175 per study arm). This sample size will also facilitate exploratory moderator and subgroup analyses to better understand which patients benefit most from the exercise program.

### Statistical analysis

Descriptive statistics will be used to characterize the study population at baseline. Questionnaire scores will be calculated according to published scoring manuals. Analyses will be performed according to the intention-to-treat principle. For the primary outcomes, mixed linear regression models will be used to assess exercise effects on physical fatigue and HRQoL separately, while taking the hierarchical structure of the data into account. Models will be adjusted for the baseline value of the outcome and stratification factors (i.e., center and therapy line). To adjust for multiple testing, the Bonferroni-Holm method will be used to maintain an overall alpha level of 5%. The same analysis will be performed for secondary outcomes. The detailed statistical analysis plan is included in the IRB study protocol.

In the economic evaluation, the balance between costs and effects of both study arms will be assessed and compared up until nine months after randomization. Results of both cost and effect measurement will be integrated using cost-effectiveness and cost-utility analyses. In the cost-utility analysis, efficiency is expressed in terms of costs per QALY. In the cost-effectiveness analysis, costs per unit of change in the two primary outcome measures will be estimated. Finally, incremental costs and incremental effects, expressed in a ratio (ICER) will be estimated. A probabilistic uncertainty analysis using bootstrapping will be performed.

To assess the potential effect of exercise on progression-free, overall, and breast cancer-specific survival, we will use Cox proportional hazard regression models stratified by center and adjusted for pre-specified prognostic factors, including therapy line, type of baseline metastases, age, and time since diagnosis of first metastases.

Potential moderators of the exercise effect will be explored (e.g., age, baseline fitness level, type of therapy, and location of metastases). In addition, mediation analyses will be performed to explore potential underlying mechanisms of exercise effects (e.g., blood markers).

Missing data due to disease progression or mortality will certainly occur, which could be Missing Not At Random (MNAR) if the exercise intervention also has an effect on progression and survival. To explore potential bias, sensitivity analyses according to EMA recommendations will be conducted using approaches that investigate different MNAR scenarios such as a pattern mixture model.

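### Optional improvement: the primary models could also adjust for three baseline prognostic factors that the plan already pre-specifies for the survival models

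*Protocol article*

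**What the plan says.** The Statistical analysis section of the protocol article specifies mixed linear models for the two primary outcomes and adds: "Models will be adjusted for the baseline value of the outcome and stratification factors (i.e., center and therapy line"). Center and therapy line are the randomization strata given under Recruitment and randomization.

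Two paragraphs later, the Cox models for progression-free, overall and breast cancer-specific survival are stratified by center and "adjusted for pre-specified prognostic factors, including therapy line, type of baseline metastases, age, and time since diagnosis of first metastases". Center and therapy line are therefore in both sets of models. Type of baseline metastases, age and time since first metastases are in the survival models only.

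On missing data the section says: "Missing data due to disease progression or mortality will certainly occur". It accepts that such data may be missing not at random if exercise also affects progression and survival, and plans sensitivity analyses such as a pattern mixture model.

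The Sample size section bases power on an "analysis of covariance (ANCOVA) adjusted for baseline values of the outcome", "assuming a correlation between pre- and post-intervention levels of Rho=0.3 or Rho=0.4".

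**The concern.** A likelihood-based mixed model is unbiased under dropout if missingness depends only on what the model contains: arm, the covariates and the observed scores. The plan expects patients to be lost through progression and death, and it names baseline factors that it regards as prognostic for those events. Three of them are not in the primary model. If they also predict fatigue or quality of life, and if their link to dropout differs by arm, the primary contrast carries a bias that measured baseline data could remove.

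There is also a question of precision. At the assumed correlations the baseline score explains 0.3² = 9% to 0.4² = 16% of the outcome variance, which leaves room for other predictors. All three factors are fixed before randomization and are needed for the survival models anyway.

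**Working it through.** **Inputs from the Sample size section:** 139 evaluable per arm, standardized effect 0.35, two-sided 2.5% per endpoint, pre-post correlation ρ = 0.3 or 0.4, dropout about 20%, 350 enrolled.

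**1. The plan's own figure.**
- Standard error = √(1 − ρ²) × √(2/139).
- ρ = 0.3: 0.9539 × 0.1200 = 0.1144, so the noncentrality is 0.35/0.1144 = 3.06.
- ρ = 0.4: 0.9165 × 0.1200 = 0.1099, so the noncentrality is 3.18.
- With 275 degrees of freedom the noncentral t gives power of 78.9% and 82.3%. The stated figures of at least 78% and 82% are confirmed.
- 278/0.8 = 347.5, against 350 enrolled.

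This calculation adjusts for the baseline score only, so the stated power does not depend on the three factors.

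**2. Adding the three factors.** Let R² be the share of residual variance that they explain. The documents give no value, so a range is shown. The residual SD becomes √[(1 − ρ²)(1 − R²)].

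| Assumed R² | Power, ρ = 0.3 | Power, ρ = 0.4 |
|---|---|---|
| 0 | 78.9% | 82.3% |
| 1% | 79.4% | 82.7% |
| 2% | 79.8% | 83.1% |
| 5% | 81.1% | 84.4% |
| 8% | 82.5% | 85.6% |

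Before rounding, the gain at 8% is 82.45 − 78.91 = 3.5 points for ρ = 0.3 and 85.60 − 82.32 = 3.3 points for ρ = 0.4. At R² = 0, three extra parameters cost less than 0.01 points, and five extra degrees of freedom leave both figures essentially unchanged.

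**3. Bias from dropout (simulation under assumptions).** The setting is about 20% missing at 6 months, the 3-month scores used, a true effect of 0.35 SD, and a prognostic factor that shifts the outcome by 0.15 to 0.30 SD per SD.
- Dropout depends on prognosis equally or modestly differently by arm: the model without the factor is off by about 0.002 to 0.011 SD.
- Strong contrast, for example dropout log-odds slopes of 1.0 in controls and 0.2 in the exercise arm: off by about 0.01 to 0.03 SD, towards a smaller exercise effect.
- With the factor in the model, the estimate returns to about 0.35 in each case.

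For scale, the standard error is about 0.11 SD, and 0.03/0.35 is about 9% of the target effect. If the 3-month scores are not used and dropout is also higher in controls, the same strong contrast gives estimates of 0.32, 0.31 and 0.29 for a factor that explains 2%, 5% and 10% of the variance. The 3-month measurement therefore already absorbs part of the problem.

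**The case against.** The strongest reply is that nothing here is wrong. Adjusting for the baseline score and the randomization strata is standard, and it goes beyond the model used for the power calculation. A different covariate set for a survival endpoint is not a contradiction. This stands in full.

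Second, the documents call the three factors prognostic for survival and nowhere say that they predict fatigue or quality of life once the baseline score is known. The one factor tied to the trial's outcomes is therapy line, in the Discussion, and it is already in the model. This also stands, and it is why the range for R² starts at 0.

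Third, there is no power shortfall. A reader might infer one from the 78.9%, but that is the per-test figure at a fixed 2.5%. Under the planned Bonferroni-Holm procedure, with both effects at 0.35, ρ = 0.3 and an assumed correlation between the endpoints of 0.3 to 0.7, per-endpoint power is about 83 to 84%, and the chance of at least one significant result is 88 to 93%.

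Fourth, a reader might infer that the plan itself expects prognosis-related dropout to differ by arm, so that the primary estimate is biased. The text does not say that. It raises an effect of exercise on progression and survival, which acts after randomization and is the reason for the planned sensitivity analyses. Baseline covariates do not resolve that mechanism.

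Two replies carry less weight. The detailed plan in the IRB protocol is not shown and may say more, but the article does state an adjustment set. The pattern mixture analyses explore departures from missing-at-random but leave the primary estimate as it is.

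**Conclusion.** The primary model as stated is valid and reaches its stated power. Including the three factors is an optional, low-cost improvement.

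The precision gain is 0 to about 3.5 power points per endpoint and rests wholly on an assumed R² of 0 to 8%. The gain in robustness is negligible (about 0.002 to 0.011 SD) unless dropout depends on prognosis quite differently in the two arms, and even then it is at most about 0.03 SD with the 3-month data used. These bias figures rest on assumed links from the factors to outcome and dropout. The documents do not support reading the omission as an error, as a loss of precision known to occur, or as a demonstrated bias.

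**What to change.** Before database lock, pre-specify that the primary mixed models adjust for the baseline value of the outcome, center, therapy line, type of baseline metastases, age and time since diagnosis of first metastases. List exactly these factors, because the Cox list is worded as open ("pre-specified prognostic factors, including therapy line, type of baseline metastases, age, and time since diagnosis of first metastases"). Set in advance the categories for type of metastases, the scale for age and time since first metastases, and a simple imputation rule for missing baseline covariates. Keep the currently stated model as a supportive analysis, and keep the planned sensitivity analyses for data missing not at random.

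The cost is a short edit to the analysis text, a few degrees of freedom and a slightly longer model. No new data are needed, since the survival models already use these factors.

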
### Data capturing and monitoring

Castor®, a cloud-based clinical data management platform, is used for randomization and data capture. Castor is also used to send out questionnaires to all participants. Validity of the data is checked by an independent monitor.

## Discussion

During palliative cancer treatment, many patients experience cancer- and treatment-related side effects that impair daily life activities and negatively affect QoL. Exercise during and after curative cancer treatment is a proven strategy to minimize these side effects. Since the majority of the available literature is in early stage cancers [9], results may not be directly generalizable to patients with advanced cancers due to the nature of the disease, differences in treatments, and the higher risk of disease progression. In the current trial, we are investigating the (cost-)effectiveness of a 9-month exercise program in mitigating fatigue and maintaining or enhancing QoL in patients with mBC.

Due to the COVID-19 pandemic, we were forced to make some (temporary) changes to the original study protocol and offer live-remote training. These changes were approved by the Medical Ethics Committee of the University Medical Center Utrecht and local ethical committees and are being reported according to the CONSERVE-SPIRIT guidelines [37]. Furthermore, the local COVID-19 regulations might result in a delay in recruitment or a cancelation of follow-up visits, since patients are not allowed or willing to visit the study center for study-related activities. All COVID-19-related changes will be reported alongside the primary results of our study.

In this study, we decided to include any patient who is currently being treated for mBC with at least a 6-month life expectancy, independent of the number of treatments received. We are aware that this approach will result in a heterogeneous, but representative, group of patients. Since the line of treatment might affect our outcomes, we stratify our randomization based on the therapy line (maximum of two treatments received versus more). Note, we decided to not include patients with oligometastatic breast cancer who are treated with curative intent

Meta-analyses of exercise-oncology trials have suggested that supervised exercise programs and programs that involve both aerobic and resistance exercises are most effective [38, 39]. In general, compliance with this exercise prescription is reported to be above 80% [40]. For patients with mBC, we anticipate that adaptations will be required, since we expect patients to present with a high disease burden and fluctuating health and performance status. This involves regular monitoring of pain and fatigue and will result in personalized adaptation of the exercise prescription. In this way, exercise intensities can be increased or decreased based on the self-reported severity of exertion. We think of such ad-hoc adaptations to the pre-planned training schedule as appropriate exercise prescription for this specific population, and not as evidence of lack of feasibility or poor intervention fidelity. A guide for selecting the appropriate exercise intensity and volumes is provided to all trainers. To improve gait stability and hence activities of daily living, balance exercises are included in the program. Balance exercises have also been suggested to improve limitations due to chemotherapy-induced peripheral neuropathies [41–44].

The skeleton is the most common site for distant metastases in breast cancer. In addition, patients can suffer from osteoporosis due to treatment with aromatase inhibitors [45]. Given the expected increased risk of skeletal-related events, including pathological fracture and spinal cord compression, exercise is often underutilized by trainers [46–48]. A recent systematic review showed that exercise is safe (no exercise-related SAEs were reported) and feasible for patients with bone metastases if it includes a supervised component [11]. In the current study, all exercise sessions are supervised by a trainer specially trained by the study team to ensure safe execution of the exercise program. Based on findings of the aforementioned review [11] and previous research in patients with advanced cancer [49], we provide all trainers with specific instructions on adaptations that need to be made to the prescribed exercise protocol in case of bone metastases. Nevertheless, exercise in patients with mBC remains challenging and additional adaptations to the exercise program may be required. Therefore, we have created an EFFECT exercise expert board that will respond to questions and request for additional information from the trainers. Additionally, members from all recruiting sites meet twice weekly to discuss exercise-related questions

In the curative setting, exercise programs from 12 weeks or longer are reported to be effective [9]. In the metastatic setting, patients generally receive continuous treatment. Therefore, we offer a longer intervention, i.e., a 6-month exercise program with 2 supervised session per week, followed by 3 months with one supervised exercise session replaced by one unsupervised session, which will be supported by an activity tracker and exercise app. Additionally, the trainer encourages the participant to be active in daily life. We hypothesize that the transition from supervised to unsupervised exercise sessions will help participants to maintain a physically active lifestyle beyond the period of study participation.

In exercise intervention studies, results might be affected by low compliance to the intervention and contamination of the control group. In order to increase attendance and compliance, our exercise sessions are individualized and supervised by specially trained and experienced trainers, and are offered close to the patients’ home. In addition, we closely monitor adherence and compliance in the study. Contamination (i.e., adoption of something similar to the intervention by the controls) is reported in 37% of all exercise-oncology trials. We took recommended measures to decrease the risk of contamination, i.e., we include relatively inactive patients, clearly explain the randomization procedure to avoid disappointment when being randomized to the control condition, and provide general exercise advice and an activity tracker to the control group [50]. While controls' physical activity level might be increased by providing the activity tracker, it has been shown that providing something to the control group decreases the risk of drop-out and of contamination [50]. Patients who consent to participate in an exercise intervention trial are generally willing to exercise, and activity trackers have been observed to provide a low-level stimulus to engage in physical activity. Thus, the EFFECT trial will assess whether the exercise intervention is significantly better than a simple low-level physical activity stimulus.

In conclusion, in the EFFECT study, we are investigating the effects of a supervised exercise program in patients with mBC on physical fatigue and QoL, as well as a range of other patient-reported, biomedical and objective health outcomes. If exercise during palliative treatment of patients with mBC is proven to be (cost-)effective, implementing exercise as an integral and standardized component of palliative care would be a logical next step. The results of our study can also inform international guidelines with respect to the role of exercise in improving the QoL of patients with advanced stages of disease and reducing cancer- and treatment-related side effects.

### Trial status

Protocol version number and date: version 4.0 dd 25-05-21

Date start recruitment: 08-01-2020

Approximate date end of recruitment: 01-09-2022

## Data Availability

The consent materials are available from the corresponding author on request. The datasets used and/or analyzed during the current study are available from the corresponding author on reasonable request.

## Abbreviations

ANCOVA: Analysis of covariance
BIA: Bio-electrical impedance analysis
BMI: Body mass index
BPI-SF: Brief Pain Inventory Short Form
CEA: Cost-effectiveness analysis
CPET: Cardiopulmonary exercise testing
DEXA: Dual-energy X-ray absorptiometry
ECOG: Eastern Cooperative Oncology Group
HIIT: High-intensity interval training
ICIQ-UI SF: International Consultation on Incontinence Questionnaire - Urinary Incontinence Short Form
iMCQ: Medical Cost Questionnaire
iPCQ: Productivity Cost Questionnaire
HRQoL: Health-related quality of life
mBC: Metastatic breast cancer
MICT: Moderate-intensity continuous training
MNAR: Missing Not At Random
MSEC: Maximal Short Exercise Capacity
PBMC: Peripheral blood mononuclear cells
PCS: Pain Catastrophizing Scale
PHQ: Patient Health Questionnaire
PSQI: Pittsburgh Sleep Quality Index
QALY: Quality adjusted life year
QoL: Quality of life
RF: Rectus femoris
RPE: Rate of perceived exertion
RPM: Revolutions per minute
RM: Repetition maximum
(S)AE: (Serious) adverse event
S-FAB: Short Fullerton Advanced Balance scale
SRT: Steep Ramp Test
VL: Vastus lateralis
